#### Monitoring:

The monitoring will be performed by the University Hospital of Clermont-Ferrand which is responsible for establishing the schedule and procedures to be followed for monitoring this study. On-site visits will be made prior to study initiation and at regular intervals during the study. Communications by telephone, telefax or mail may be used as needed to supplement site visits.

Prior to the beginning of this study, the Investigator will be informed as to the anticipated frequency of the monitoring visits. In addition, the Investigator will receive reasonable notification prior to each monitoring visit during the course of the study.

The purpose of these visits is to verify:

- Adherence to the protocol,
- Availability of completed ICFs and adequate consent process
- Completeness and accuracy of the e-CRFs, and study related source document.

At each visit, the Investigator will be expected to cooperate with the monitor for the review and verification of all e-CRFs, the study drug supply and inventory records and any additional records as may have been previously arranged.

At the pre-study visit, the study monitor and/or the Sponsor representative will check that the Investigator has the technical means and the staff to carry out the study with regards to availability, subject recruitment, facilities and environment.

Prior to the start of the study, the Sponsor Study Manager will ensure that he/she has received the following information:

- Study protocol and financial agreement signed by all parts;
- Written statement of the CPP approval;
- Curriculum vitae of the investigators;
- Approval by the Competent Authority; ANSM.

As well as all other documents required for study initiation, as per GCP.

During the study, adherence to the protocol, availability of signed ICFs and conformity of the data entered in the e-CRF with the source documents will be checked at appropriate intervals by the study monitor.

At the end of the study, the Sponsor study manager will ensure he has received:

- The completed e-CRFs;
- All unused medications and remaining packaging, or those they have been destroyed in accordance with the applicable regulations.
- All documents are properly filed in the Investigator's site file as per GCP.

## **Ethics and dissemination**

### Research ethics approval:

The protocol, information and consent form (ICF) and the e-CRF of the study will be submitted for opinion to the ethic committee (CPP VI of the Rhône-Alpes-Auvergne region) which carries the principal investigator of this trial. Notification of the approval of the CPP will be sent to the study sponsor and competent authority (ANSM). An authorization request will be made by the promoter to ANSM before the start of the study.

When necessary, the protocol amendments will also have to be submitted to the above mentioned CPP or ANSM either for information or for formal approval. With the exception of emergency situations, no changes or deviations in the conduct of this protocol will be permitted without the documented approval of the Sponsor. The IEC as well as the French Health Authorities which granted original approval for the study must be notified of all changes in the protocol and must provide documented approval for any change or deviation which may increase the risk to the subject and/or which may adversely affect the rights of the subject or validity of the investigation. This stipulation does not apply to those changes made to reduce discomfort or risk to subjects or which are purely administrative in nature.

In the event of any emergency, the Investigator shall institute any medical procedures, which he/she deems appropriate. However, all such procedures must be promptly reported to the Sponsor.

Amendments that are substantial and are likely to have an impact on the safety of trial subjects, or are otherwise significant, should receive IEC/Competent Authority approval. If the opinion of the IEC is favourable and the Competent Authorities have raised no grounds for unacceptability the study can be conducted according to the amended protocol. Non substantial amendment should only be notified.

### Consent or assent:

Voluntary written ICF must be obtained from each subject prior to performing any study related procedures in compliance with the recommendations of the Declaration of Helsinki.

Subject should not be screened or treated until the subject has signed an approved ICF written in a language that is understandable to the subject.

Each subject should be given both verbal and written information describing the nature and duration of the clinical study. The ICF should be signed and personally dated in two originals by the subject and the person who conducted the informed consent discussion. The

Investigator, or the attending physician, will explain the nature, purpose and risks of the study. The subject will be informed that he has the right to withdraw at any time from the study, without giving reasons. In this case, the subject will not receive any indemnity. The informed consent process should take place under conditions where the subject has adequate time to consider the risks and benefits associated with his participation in the study.

The Investigator is responsible for assuring the appropriate content of the ICF and that informed consent is obtained from each subject in accordance with all applicable regulations and guidelines. The ICF will be reviewed and approved by the Sponsor, and then submitted to the IEC.

Each subject should receive one original of the signed and dated written ICF and any other information provided to the subject.

The second original of the signed and dated ICF should be retained in the Investigator's file.

The Investigator should maintain a log of all subjects who sign the ICF.

#### Declaration of interests:

No competing interests.

#### Access to data:

The promoter is responsible for obtaining the agreement of all parties involved in research in order to guarantee direct access to all places of conduct research, source data, source documents and reports in a goal quality control and audit by the sponsor.

The investigators will make available documents and individual data strictly necessary monitoring, quality control and auditing of biomedical research, available to people with access to these documents in accordance with legislative and regulatory provisions (Articles R.5121-13 L.1121-3 and the code of public health).

#### Ancillary and post-trial care:

If the patient is at the waning of the study indicates a marked improvement in his symptoms, unblinding procedure will be permitted to determine the drug to be prescribed after the study. Unblinding procedure, randomization plan and packaging of therapeutic units will maintain intact the double blind until the end of the study. Patients will be referred to their general practitioner or a specialist pain doctor who will be informed of the treatment received by the patient during the study. Note that the requirement in Zarontin® or placebo for the treatment of pain related to IBS being out of their marketing authorization framework,

the sponsor does not support a continuation of treatment after the study. No patient follow-up is planned after the study.

Dissemination policy:

The data set will be propriety of the sponsor (CHU Clermont-Ferrand). However, the principal investigator (MD) and the project manager (NK) will have a full access to the final data set. The results will be published in a peer-reviewed journal, presented at international congresses and completed online on ClinicalTrials.gov.

# APPENDICE 3 – BIOLOGICAL SPECIMEN

| Blood Test       | Time             |
|------------------|------------------|
| ALT              | D0-7 (screening) |
| AST              | D0-7 (screening) |
| ALP              | D0-7 (screening) |
| GGT              | D0-7 (screening) |
| Creatininemia    | D0-7 (screening) |
| Haematocrit      | D0-7 (screening) |
| Beta-HCG         | D0-7 (screening) |
| Genetic analysis | D0-7 (screening) |

## 1. Trial summary

### 1.1 Primary objective

To evaluate the efficacy of ethosuximide versus placebo, administered in add-on therapy, on intensity of abdominal pain related to IBS and to evaluate the score of the Subject Global Assessment of Relief (SGA scale) after 12 weeks of treatment.

### 1.2 Secondary objectives

The secondary objectives concern the effects of ethosuximide on:

- ▶ the severity of IBS symptoms
- ▶ the quality of life (physical and mental)
- ▶ the safety of ethosuximide.

The study discontinuation rate and analgesics and transit regulator consumption were assessed throughout the study.

### 1.3 Trial design

Multicentre, national, randomised, double-blinded, placebo-controlled, parallel group clinical trial with two parallel groups:

- Group A: ethosuximide
- Group B: placebo

### 1.4 Randomization

After patient informed consent was obtained and eligible criteria respected, enrolled patients were randomly allocated to receive either ethosuximide or placebo in a 1:1 ratio. Randomisation was conducted over a dedicated, password-protected, SSL-encrypted website (CSOnline, Clinsight) to allow concealed allocation. Each patient was given a unique patient number and randomisation number.

Computer-generated random numbers was used to generate allocation sequence with stratification by centre and a 6-block random sequence. Sequentially numbered containers were used to implement the random allocation sequence.

### 1.5 Blinding

Participants were given blinded medication. Trial medication (syrup of ethosuximide or placebo) were visually identical and packaged into indistinguishable bottle by the pharmacist of the coordinating centre and delivered to each specific study site. Only the pharmacy of the study coordinating centre was aware of the bottle composition (coding list). The receipt, storage and dispensing of the blinded trial medication were conducted by the pharmacy department in each individual study site.

The allocation of trial medication was determined by the web-based randomisation system. Each study site had sufficient bottles to be allocated to patients included.

The allocated trial medication was blinded to the patient, the clinical staff caring for the patient, the investigators, the outcome assessors, the data manager, and the statistician conducting the analyses. At each participating centre, data were collected and entered into the web-based electronic case report form (eCRF) by trial or clinical trained personal (clinical research associate), blinded to the allocation group, under the supervision of the trial site investigators.

### 1.6 Eligibility criteria

#### 1.6.1 Inclusion criteria

- ▶ Man or woman aged 18 years or more.
- ▶ Negative pregnancy test and effective contraception.
- ▶ IBS defined by ROME IV criteria.

- ▶ Treatment failure (11-point NRS abdominal pain  $\geq 4/10$ ) for at least 3 months despite stable treatment for a month, if any.
- ▶ Patients affiliated to the regime of the French Social Security.
- ▶ Patients able to deliver a free and informed consent.

#### 1.6.2 Non-inclusion criteria

- ▶ Breastfeeding.
- ▶ Diabetic patients.
- ▶ Chronic pain of greater intensity than the pain related to IBS.
- ▶ Renal or hepatic impairment defined by significant liver function (liver enzymes  $>3 \times$  normal values, cholestasis) and renal (modification of the diet in renal disease (MDRD)  $<60$  mL/min) abnormalities.
- ▶ Current or history of severe depression (hospitalisation, long-term antidepressant treatment).
- ▶ Addiction to alcohol and/or drugs.
- ▶ Patient already treated with antiepileptic.
- ▶ Epilepsy.
- ▶ Allergy to succinimide (ethosuximide, methsuximide, phensuximide).
- ▶ Psychotic disorders.
- ▶ Insufficient cooperation and understanding to adhere strictly to the conditions provided by the study.
- ▶ Patients undergoing a measure of legal protection.

#### 1.7 Sample size

According to previous work presented in literature, we have estimated that a sample size of  $n=130$  patients per randomised group, for a two-sided type I error at 5%, would provide 90% statistical power of detecting an absolute difference of 20% between ethosuximide and placebo in the primary outcome. Based on the meta-analysis of Ford et al, the estimated median responder rate in the placebo group was 35%. A slightly higher rate than the previously mentioned meta-analysis (32% of responders under drug therapies), in order to avoid underestimating the placebo effect. Finally, a total of  $n=290$  patients (145 by group) was considered to take into account lost to follow-up (10%). A blinded interim analysis was planned after enrolment of the first 100 patients using the Lan and DeMets rule (East software, Cytel, Cambridge, Massachusetts, USA) to study safety of study treatment (ethosuximide and placebo) and efficacy, to continue or stop the study in case of futility and to recalculate the number of patients needed. The type I error is fixed at 0.03 for this interim analysis.

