#### Sample size:

According to previous work presented in literature, we have estimated that a sample size of  $n = 130$  patients per randomized group, for a two-sided type I error at 5%, would provide 90% statistical power of detecting an absolute difference of 20% between ethosuximide and placebo in the primary outcome: rate of responders to treatment as defined previously (35% for placebo and 55% for ethosuximide). Finally, a total of  $n=290$  patients (145 by group) will be considered to take into account lost to follow-up (10%). An interim analysis will be performed after 100 included patients to analyse safety and effectiveness in order to recalculate the sample size according results.

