##### *Statistical methods*

Statistical analyses will be conducted using Stata software (version 13, StataCorp, College Station, US). A two-sided p-value of less than 0.05 will be considered to indicate statistical significance (except interim analysis).

Intent-to-treat (ITT), mITT, and per-protocol (PP) analyses were performed for the primary endpoint and expressed as relative risks (RR) with 95% confidence intervals (CI). Non-compliant patients were considered non-responders. Responder rates were compared using the chi-squared test and a pre-specified multivariate analysis was performed using a generalized linear mixed model (Poisson regression with a log link and robust variance 26) accounted for fixed covariates (e.g., gender, IBS subtype) and centre-level variability were performed. Primary endpoint components were also analysed with the Hochberg procedure for multiple testing.

Continuous outcomes were assessed with linear mixed models incorporating patient-level random effects (slope and intercept) nested within centre-level random effects. Results were expressed as regression coefficients (standardized mean differences - MD) with 95% CI, based on the interaction between time and randomization group. The normality of residuals from these models was analysed as aforementioned. Safety analysis was conducted with chi-squared or Fisher's exact tests.

Missing data (if any) were imputed using Multiple Imputation by Chained Equations (MICE). Analyses were conducted using Stata 15.0, with a two-sided P value <0.05 considered significant, and the widths of confidence intervals were not adjusted for multiplicity and should not be used as a substitute for hypothesis testing, except for the primary outcome and its composite components. An interim analysis is planned after enrolment of the first 100 patients using the Lan and DeMets rule (East software, Cytel Inc, Cambridge, Massachusetts, US). The type I error is fixed at 0.03 for this interim analysis. In addition, an early intermediate analysis (third of the inclusions) will be also proposed in order to study safety of the initial maximum dose (10 ml/day) and, if necessary, to allow the addition of a therapeutic dose in case of inefficiency.

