Planned subgroup analyses were assess heterogeneity of the effect of ethosuximide on the primary outcome measure in pre-specified subgroups of patients with IBS subgroup and gender. According to usual recommendations, the interactions between group randomization and subgroups was evaluated in regression models (i.e., random-effects models, linear or generalized linear).

A descriptive analysis of stopping and discontinuations in view of dose escalation was considered. A particular focus was done to safety and lose to follow-up. A study of abandonment considered as censored data was proposed using the Kaplan-Meier estimation. The proportional-hazard hypothesis was verified using Schoenfeld's test and plotting residuals.

Finally, a sensitivity analysis was performed and the nature of missing data was studied (missing at random or not). According to this, the most appropriate approach to the imputation of missing data was proposed (MICE, spline interpolation, LOCF, BOCF...).

A two-sided P value of less than 0.05 was considered for statistical significance of all analyzes. The Hochberg procedure was used to adjust for multiple testing of each component of the composite primary outcome ((1) decrease of at least 30% of the intensity of abdominal pain (11-point NRS) compared with the score before treatment and (2) significant global improvement defined by a score of 4 or 5 on the SGA scale). Because of the potential for type 1 error due to multiple comparisons, findings from analyses of secondary endpoints were interpreted as exploratory.

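### The interim is labelled blinded but carries a between-arm rule, and testing at 0.03 and then at 0.05 does not keep the stated 5% type I error

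*Combined protocol and SAP*

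**What the plan says.** SAP 1.7 introduces the look with "A blinded interim analysis was planned after enrolment of the first 100 patients using the Lan and DeMets rule". Besides safety, its purposes are "and efficacy, to continue or stop the study in case of futility and to recalculate the number of patients needed". The section adds: "The type I error is fixed at 0.03 for this interim analysis".

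The protocol's Sample size section puts it this way: "An interim analysis will be performed after 100 included patients to analyse safety and effectiveness in order to recalculate the sample size according results". Its Statistical methods section repeats the Lan-DeMets rule and the 0.03. Neither protocol section calls the look blinded.

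For the final analysis, SAP 2.4 states "A two-sided P value of less than 0.05 was considered for statistical significance of all analyzes". The protocol has "A two-sided p-value of less than 0.05 will be considered to indicate statistical significance (except interim analysis", which exempts the interim but leaves the final test at 0.05. SAP 2.3 specifies an unadjusted chi-squared or Fisher's exact test.

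SAP 1.5 includes among those blinded to allocation "the data manager, and the statistician conducting the analyses", and SAP 2.1 schedules all analyses before the code is broken.

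The documents give no spending function, final boundary, futility threshold, re-sizing rule, cap on sample size or independent body for the interim. All three descriptions of the look count patients enrolled or included. None requires a week-12 outcome.

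**The concern.** A Lan-DeMets rule with an error level belongs to a test between arms. If blinded means that the arms are pooled, there is no such test to perform. If it means masked labels, the test can be done, but part of the 5% is then spent at the interim and the final level must be lower than 0.05. The documents do not lower it.

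The re-sizing adds a second, separate route to error. If the new sample size depends on the observed difference and the accumulated data then go into an ordinary chi-squared test, that test no longer has its nominal level.

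At stake is the meaning of the primary p-value. There is also a question of information. The endpoint is read at week 12, so a look triggered by enrolment may rest on far fewer than 100 outcomes.

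**Working it through.** **Inputs.** Responder rates 35% and 55%, two-sided 5%, 90% power, 130 per arm, 290 in total after 10% loss (protocol Sample size; SAP 1.7). Interim at 100 patients with level 0.03 (SAP 1.7; protocol Statistical methods). Final level 0.05 (SAP 2.4; protocol Statistical methods). At least ten centres at 1 patient per month each (protocol Enrolment).

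**1. The plan's own figure.** n per arm = [1.960·√(2·0.45·0.55) + 1.2816·√(0.35·0.65 + 0.55·0.45)]² / 0.20² = (1.379 + 0.883)² / 0.04 = 127.9, so 128. With 130 per arm the power is 90.5%. Then 130/0.9 = 144.4, so 145 per arm and 290 in total. The stated size is reproduced. It is a fixed design with no allowance for an interim test.

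**2. Overall type I error at 0.03 then 0.05, fixed sample size.** The interim and final statistics Z₁ and Z₂ are bivariate normal with correlation √t, where t is the information fraction. Overall error = 1 − P(|Z₁| < 2.170 and |Z₂| < 1.960).

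| t | Overall error | Final level that restores 5% if 0.03 is spent |
|---|---|---|
| 100/290 = 0.345 | 7.15% | 0.0255 |
| 100/260 = 0.385 | 7.06% | 0.0262 |

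At a final level of 0.0255, 130 per arm gives about 85% power at the final test alone, ignoring rejections at the interim.

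**3. Does naming Lan-DeMets explain the 0.03?** At t = 0.345 to 0.385:

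- O'Brien-Fleming-type spending, 2 − 2Φ(1.960/√t), gives 0.0008 to 0.0016 and leaves a final level of 0.0496 to 0.0493.
- Pocock-type spending, 0.05·ln(1 + (e − 1)t), gives 0.023 to 0.025 and leaves 0.032 to 0.031. It reaches 0.03 only at t of about 0.48.

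Neither standard function produces 0.03 at this look.

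**4. Re-sizing.** Simulation with no true effect: 50 per arm at the interim, sample size recalculated for 90% power, then a chi-squared test of all data at 0.05. The null rates were 35% and 45%. For re-sizing on the observed difference, the floor was either 51 or 130 per arm and the cap 1.5 to 4 times 130. Floors and caps are assumptions, because the plan gives none.

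| Rule | Type I error |
|---|---|
| Re-size on observed difference, no interim rejection | 5.3% to 6.9% |
| Re-size on observed difference, with rejection at 0.03 | 7.6% to 8.6% |
| Re-size on pooled rate only | about 5.0% at the 35% null rate; 5.1% to 5.4% at 45% |

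With 130 per arm and no interim, the same chi-squared test runs at 5.0% at the 35% rate and 5.3% at the 45% rate, because the data are discrete. So the 5.3% at the low end of the first row, found at the 45% rate, is not inflation from re-sizing, and pooled-rate re-sizing adds essentially nothing.

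**5. Trigger.** Ten centres give 10 patients per month. Twelve weeks is 12·12/52 = 2.77 months, so 27.7 patients enrol within the last 12 weeks. About 72 of the first 100 have reached week 12 when the 100th enrols, before dropout (about 58 with 15 centres, an assumption). With 36 per arm the 95% half-width for the difference is 1.96·√(0.475/36) = 22.5 points. With 50 per arm it is 19.1. The target difference is 20 points.

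**The case against.** **Masked labels.** A reader might infer that the interim cannot be run as written. The documents do not support that. SAP 1.5 and 2.1 use blinding to mean that the analyst does not know the allocation and that analyses precede code-breaking. A two-sided boundary is symmetric and can be applied to arms labelled A and B. This stands. It does not rescue the error rate, because inflation comes from using the between-arm difference, not from knowing which arm is which. For the same reason it would be wrong to say that the inflation arises only if the look is unblinded.

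**No efficacy stop is stated.** The only stop named is for futility, and a futility stop alone does not raise type I error. This stands as a limit: rejection at the interim is inferred from the Lan-DeMets rule and the 0.03, which would otherwise have no function.

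**Re-sizing may be harmless.** The texts do not say which quantity drives the recalculation. A pooled responder rate or the loss rate would fit. This also stands, so the re-sizing figures are conditional.

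**The final level may be adjusted in the software.** A Lan-DeMets design would normally supply a reduced final boundary. But neither document states one, and both state 0.05.

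**The trigger may describe a cohort.** The first 100 patients could be analysed once they have been followed up. That is possible and would solve the information problem, but the plan does not say so. Even at 72 outcomes the look is weaker, not impossible.

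**Staff could infer the interim effect from a new sample size.** This would need a known effect-based rule, and the documents contain none.

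**Conclusion.** Wrong as written. No reading of SAP 1.7 combines all its elements with a 5% error rate. On pooled data the Lan-DeMets test cannot be done. On between-arm data, masked or not, the stated levels exceed 5%.

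The main figure is 7.1% to 7.2% overall at fixed sample size. It rests on one inference, that 0.03 permits rejection at the interim. The figures involving re-sizing rest on a further assumption, that the observed difference drives the recalculation, and on assumed floors and caps. The two sources are separate: most of the combined 7.6% to 8.6% comes from the 0.03 and 0.05 levels. The enrolment trigger is a lesser defect, and its size depends on the number of centres and on when the data are cut.

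**What to change.** 1. **Re-size blind.** Recalculate only from the pooled responder rate, keep the 20-point difference, and set a cap.
2. **If a between-arm look is kept,** have a statistician outside the trial team run it. Name the spending function and derive the final level from the alpha actually spent: about 0.0255 at t = 100/290 if 0.03 is spent, or close to 0.05 with O'Brien-Fleming-type spending. State whether rejection for efficacy is allowed. Make futility non-binding and give its threshold. Allow no re-sizing on the observed effect unless the final statistic uses stage weights fixed in advance.
3. **Trigger on outcomes.** Hold the look when 100 patients have reached or missed the week-12 endpoint.
4. **Align the texts.** Say in both documents what blinded means for this look and who sees its results, and replace the final 0.05 with the derived level.

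The cost is a wording change in the protocol and SAP and an interim about 12 weeks later, with about 128 patients enrolled by then at ten centres. Blinded re-sizing cannot react to an effect smaller than planned. Keeping 0.03 at the interim would need 151 per arm instead of 128 for 90% power at the final test alone, whereas O'Brien-Fleming-type spending costs almost nothing.
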